### Randomization and assessor blindness

Treatment allocation is randomized via a computerized randomization plan (no stratification factors) and performed observer-blind. Extensive steps are taken to ensure rater blindness. The randomization plan is only accessible to the study coordinators, thus reducing the risk that assessors may be accidentally unblinded. Patients are informed that they are not to disclose their group assignment and are reminded of this at every testing session. At the end of the baseline testing session, all participants meet with a member of the research team who is not involved in testing and has access to the site-specific randomization list. This individual gives the participant an envelope in which intervention assignment is identified. Raters are not involved in the active intervention. Rater blinding is verified by asking the rater to guess the participant’s treatment allocation at the beginning of every testing session and indicating their certainty.

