#### Intervention

To ensure comparability of results, both interventions are implemented for the same duration (6 weeks; 12 sessions) and frequency (45–60 min per session). Psychologists undergoing post-graduate training provide both MCT+ and computerized CR. All MCT+ trainers completed a 2-day MCT+ workshop and receive regular intervision from two of the authors of the MCT+ therapy program (RV, FB).

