##### Cognitive remediation

MyBrainTraining^©^ (BBG Entertainment GmbH) [76] is a newly developed computer-based cognitive remediation program, which aims to improve cognitive functioning deficits present in schizophrenia by presenting a series of cognitive exercises, which are repeatedly practiced. In the present study, participants complete all exercises independently. The program consists of thirty exercises aimed at training executive functioning through different types of tasks, including those of vision, arithmetic, logic and memory. All exercises are conducted on PC’s over the Internet. The exercises were designed during the development of the “Train your Brain with [name]” program in cooperation with the Industry University Research Project and [name]. [name].

Based on the participant’s performances, the difficulty of each task automatically increases or decreases. The exercises are similar to video games and include fun or motivational elements. The administrator has the ability to determine specific training plans and to adapt exercises to each patient’s needs (e.g., level of difficulty, varied time limits, etc.). Data protection and security comply with industry standards.

For the present study, participants are asked to complete the exercises in a specific order and are provided with feedback from the program on their performance, which they record on an exercise log. Log-in information is not shared with participants to prevent practice at home. Like the MCT+ group, three months after the final session participants are sent a postcard asking if they are still using the skills learned while completing MyBrainTraining^©^ and if they have continued cognitive exercises using other modalities (e.g., crossword puzzles, Sudoku, etc.).

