**Fig. 1 Fig1:**
[figure not shown]
Study flow

Using calculation software PASS 2008 [77] with a conventional alpha level of .05 and a beta-value of .20 for a two-tailed test, it was calculated that each group must be comprised of 130 patients to detect a small to medium effect (*d* = 0.35) at the 6-month follow-up testing. Assuming a dropout rate of 20 % (including dropout due to non-compliance and loss to follow-up), the study will be conducted with a sample size of 328 patients or 82 patients per trial center.

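### Allocation runs from site-specific lists, but the text denies stratification and the named ANCOVA covariates omit centre; possible therapist clustering in MCT+ also deserves a prespecified robustness analysis

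*Protocol article*

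**What the plan says.** Under Randomization and assessor blindness, the protocol article states that allocation is made "via a computerized randomization plan (no stratification factors". A few sentences later, the team member who gives the patient the assignment "has access to the site-specific randomization list". Whether the lists are blocked is not stated. The Participants section names four clinics, and the Sample size section says that "the study will be conducted with a sample size of 328 patients or 82 patients per trial center".

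The Statistical analyses section specifies an ANCOVA and names its covariates: baseline level, antipsychotic dose and concurrent treatment. Centre and therapist are not among them, and the only sensitivity analysis described concerns missing values.

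On delivery, the Intervention section says: "Psychologists undergoing post-graduate training provide both MCT+ and computerized CR". The MCT+ section lets the trainer choose, extend or skip units, partly by the trainer's own preference. For the control arm, the Cognitive remediation section says: "In the present study, participants complete all exercises independently".

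The power calculation uses a "conventional alpha level of .05 and a beta-value of .20 for a two-tailed test" and concludes that "each group must be comprised of 130 patients to detect a small to medium effect" (a standardised difference of 0.35). It has no design effect.

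**The concern.** A separate list for each site is, in effect, stratification by centre, whatever the text calls it. A trial is ordinarily analysed by the groups within which it randomised. If allocation is balanced within centre and centre is left out of the model, between-centre variance stays in the residual although it does not contribute to the error of the treatment comparison. The standard error is then too large and some power is lost. The article itself regards centre as potentially relevant: its Discussion gives reducing allegiance effects as a reason for adding centres.

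Therapist works in the other direction. MCT+ is delivered one-to-one with room for individual choice, while control patients work alone at a computer. If patients of the same MCT+ therapist have correlated outcomes and the analysis treats them as independent, the standard error can be too small. A borderline positive result would then be hard to separate from the performance of a few therapists.

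**Working it through.** **Inputs from the protocol article.** Two-sided alpha 0.05, power 0.80, d = 0.35, 130 evaluable patients per arm, 20% dropout, total 328, four centres of 82.

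**Inputs assumed, because the article does not give them.** Share of outcome variance due to centre: 0.05 and 0.10. Number of MCT+ therapists k: 8 to 24 (130/24 = 5.4 to 130/8 = 16.3 analysed patients each). Therapist ICC: 0.01 to 0.10.

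**1. The plan's own figure.** The normal approximation n = 2(1.960 + 0.842)²/0.35² gives 129 per arm after rounding up; the t-test gives 129.1, hence 130. At 130 per arm the standard error is √(2/130) = 0.124, the standardised effect is 0.35/0.124 = 2.822, and power is Φ(2.822 − 1.960) = 0.806 (t-test 0.803). Dropout: 260/0.8 = 325, or 326 if each arm is rounded up; the next multiple of four is 328 = 4 × 82. The figure reproduces, for independent patients.

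**2. Centre omitted, lists balanced within site.** The ratio of true to reported standard error is r = √(1 − R²), where R² is the share of outcome variance due to centre. Type I error = 2[1 − Φ(1.96/r)]. Power with centre omitted = Φ((2.822 − 1.96)/r). Power with centre in the model = Φ(2.822/r − 1.96).

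| R² | r | Type I error, omitted | Power, omitted | Power, adjusted |
|---|---|---|---|---|
| 0.05 | 0.975 | 0.044 | 0.812 | 0.825 |
| 0.10 | 0.949 | 0.039 | 0.818 | 0.845 |

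The gain from adjusting is 0.825 − 0.812 = 1.3 points and 0.845 − 0.818 = 2.7 points. If the site lists are simple unblocked sequences, chance imbalance between centres is part of the real error. Omission then does not bias the standard error in this way and costs only precision.

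**3. Therapist clustering in MCT+ only.** The design effect in that arm is DE = 1 + (130/k − 1)·ICC. The variance of the difference is (DE + 1)/130, so the true standard error exceeds the reported one by the factor s = √((DE + 1)/2). Type I error of the unadjusted test = 2[1 − Φ(1.96/s)]. Power with the correct standard error = Φ(2.822/s − 1.96).

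| k | ICC | DE | s | Type I error | Power |
|---|---|---|---|---|---|
| 24 | 0.01 | 1.044 | 1.011 | 0.053 | 0.797 |
| 24 | 0.05 | 1.221 | 1.054 | 0.063 | 0.764 |
| 24 | 0.10 | 1.442 | 1.105 | 0.076 | 0.724 |
| 16 | 0.01 | 1.071 | 1.018 | 0.054 | 0.792 |
| 16 | 0.05 | 1.356 | 1.085 | 0.071 | 0.739 |
| 16 | 0.10 | 1.712 | 1.165 | 0.092 | 0.678 |
| 8 | 0.01 | 1.153 | 1.037 | 0.059 | 0.776 |
| 8 | 0.05 | 1.763 | 1.175 | 0.095 | 0.670 |
| 8 | 0.10 | 2.525 | 1.328 | 0.140 | 0.566 |

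**4. Other therapist structures.** With separate therapists in each arm, 8 to 24 per arm and ICC 0.05, s = √DE; type I error is 0.076 to 0.140 and power 0.72 to 0.57. If the same therapists serve both arms with an equal effect in each, their effects largely cancel in the comparison. A simulation of 4,000 runs (four centres of 65 analysed patients, 16 therapists, ICC 0.05) gave a type I error of 0.047 in that case, against 0.079 with therapist effects in MCT+ only. The formula value for the latter is 0.071, and the Monte Carlo error is about √(0.071 × 0.929/4000) = 0.004.

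**The case against.** The statement that there are no stratification factors may mean only that no patient characteristics were used within each site's list. That reading is possible, but the text should then say so, because taken literally the two statements conflict.

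A journal article condenses the full plan, and the covariate list is introduced as a means of exploring influences on outcome; it is not said to be exhaustive. A fuller analysis plan could contain centre and therapist terms. This limits the point to the model as the article states it. The article does, however, commit to a model and name its covariates, so it is fair to ask that they follow the allocation.

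Three stronger readings are tempting, and the article does not support them.

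- A reader might infer that omitting centre makes the test conservative. That requires balance within site, and blocking is not stated.
- A reader might infer that outcomes cluster by therapist in one arm only. Solitary computer work in the control arm makes this plausible, but psychologists provide both interventions, and whether the same ones serve both arms is left open. Features that may limit therapist variance also count: a manual, a two-day workshop, regular intervision, adherence ratings and required units.
- A reader might infer that the trial does not have its stated 80% power, or that 130 per arm is an error. The arithmetic is right under independence. At 24 therapists and ICC 0.01, power is still 0.80 and type I error 0.053; the values 0.57 and 0.14 belong to the least favourable corner of an assumed range.

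**Conclusion.** The two statements on allocation need reconciling, and the named model should include centre. This rests on the text and needs no assumed figure. The numerical consequence is modest: no excess of false positives from omitting centre and, with balanced lists and the assumed centre shares, about 1 to 3 points of power.

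Therapist clustering is a secondary, conditional point. It could matter more than centre, and in the opposite direction, but its size cannot be derived from the article; it ranges from negligible to material with the number of therapists, the ICC and the overlap between arms. Nor can the net direction of the two omissions together be fixed. What can be said is that the 80% power is conditional on independent patients and that the article names no analysis to test that condition.

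**What to change.** 1. Reword the randomisation section to say that allocation runs within centre, and state whether the site lists are blocked.
2. Add centre as a fixed factor to the primary model and to all analogous models.
3. Prespecify a robustness analysis with a random therapist effect, using therapist ID. Nest it in the MCT+ arm only if therapist effects arise only there; if therapists differ by arm, include it in both. Report the estimated ICC.
4. State how many therapists there are and whether they serve both arms, and note beside the 80% power that it assumes independent patients.

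The cost is three degrees of freedom for centre, one ID variable (the article does not say whether it is already recorded) and one extra analysis. The sample size of 328 need not change. Recruitment was still open when the article was submitted, and therapist ID is easier to capture during treatment than to reconstruct afterwards.

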#### Outcome measures

##### Selection and diagnostic measures

The Mini-International Neuropsychiatric Interview 5.0 (German version) [54], a short, structured diagnostic interview based on DSM-5 criteria, will be conducted to assess specifically for psychosis, affective disorder with psychotic features, substance use disorders and suicidality. It is fully structured to allow administration by non-specialized interviewers. The agreement between the M.I.N.I. and the Structured Clinical Interview for DSM-IV (SCID) is good or very good for most diagnoses. Test-retest reliability is also good (kappa = .75).

##### Primary outcome measure

The PSYRATS is a commonly used semi-structured interview that measures quantitative and qualitative aspects of delusions and hallucinations, including preoccupation, conviction and distress. The difference in PSYRATS delusions subscale score from baseline to follow-up serves as the primary outcome parameter. The validity of the PSYRATS has been demonstrated in chronically psychotic patients and it has been shown to have good psychometric properties [56]. Unlike the PANSS, which collapses important aspects of positive symptoms (e.g., delusion conviction and distress), the PSYRATS allows for a multivariate assessment of delusions and, the PSYRATS is highly correlated with the PANSS.

##### Secondary outcome measure

The Positive and Negative Symptoms Scale (PANSS) is a 30-item scale that assesses positive, negative and general psychopathology based on a semi-structured interview. The PANSS has good psychometric properties and is sensitive to change [57].The Fish Task [58] is a computerized variant of the classical Beads Task. In this measure, participants are shown two lakes containing orange and gray fish (e.g., lake A with 80 % orange and 20 % gray fish, and lake B with the reverse ratio). Ten fish are successively presented in a predetermined sequence to the participant. After each draw, the participant indicates whether they can make a decision regarding the origin of the fish. All fish drawn remain visible throughout the task in order to minimize working memory demands. Parallel versions are used across the testing sessions to reduce practice effects. The presence of a jumping to conclusions bias is defined as reaching a decision after drawing only one or two fish. The key variable of interest is the number of draws to decision.The Negative Symptom Assessment (NSA-4) [59] is an instrument to rapidly assess negative symptoms based on a rating by the interviewer, which includes four items (restricted speech quantity, reduced emotion, reduced social drive, and reduced interests). Each item is rated by the interviewer on a scale from ‘1’ to ‘6’ where ‘1’ represents no reduction from normal behavior and ‘6’ represents severe reduction in or absence of the behavior, with markedly impaired functionality. Consistency of ratings by experts has been shown to be high [60].The Patient Health Questionnaire-9 item (PHQ-9) [61] is a self-report measure of depression, which is a module of the full Patient Health Questionnaire. Each item is rated based on the presence or absence of the symptom over the past 2 weeks for a total possible score of 27. Mild depression is likely at a score of 5, while the cutoff for severe depression is 15. Internal reliability (Cronbach’s α = .89) and test-retest reliability (*r* = .84) of the scale are excellent.The Calgary Depression Scale for Schizophrenia (CDSS) [62] is a brief semi-structured interview scale, which allows raters to assess depressive symptoms separate from positive, negative and extrapyramidal symptoms in people with schizophrenia. The nine items of the scale are rated on operational criteria from ‘0’ to ‘3’. The scale is correlated with other depression rating scales (Hamilton Depression Rating Scale and the Beck Depression Inventory). Internal reliability is good (Cronbach’s α = .79) [63].The World Health Organization Quality of Life - BREF (WHOQOL-BREF) [64, 65] is a self-report measure of overall life satisfaction. The measure assesses quality of life in four domains: physical, psychological, social and environment. Internal consistency assessed internationally across several study centers for most scales is good (Cronbach’s α > .70).The Rosenberg Self-Esteem Scale (RSE) [66] is a widely used 10-item self-report measure that assesses global self-esteem. Internal consistency (Cronbach’s α = .84) as well as split-half reliability (*r* = .74) of the German version are good.The Beck Cognitive Insight Scale (BCIS) [67] measures self-reported ability to distance oneself from and reflect upon subjective cognitive biases. The 15-item measure is comprised of two subscales: self-reflectiveness and self-certainty. Insight plays an important role in the formation and maintenance of psychotic symptoms. Internal consistency among individuals with schizophrenia is acceptable (Cronbach’s α = .60 – .68). In Beck’s initial study, the mean self-reflectiveness score for patients without a psychosis diagnosis did not significantly differ from those without a psychosis diagnosis while self-certainty was higher among those with a psychosis diagnosis in comparison to patients without a psychosis diagnosis [67].The Personal and Social Performance Scale (PSP) [68] is a semi-structured clinician-rated interview of social functioning over the past 30 days in individuals with schizophrenia. The PSP rates functioning on four subscales: socially useful activities, personal and social relationships, self-care, disturbing and aggressive behavior. Descriptive anchor points (I = absent; VI = very severe) are used to rate patient functioning in these domains. An overall functioning score is then derived from the subscale scores. Inter-rater reliability is acceptable (Cohen’s κ = .68).The Short Form-12 (SF-12) [69] is a short self-report questionnaire used to measure functional health and well-being. The SF-12 has been shown to distinguish individuals with severe mental illness from the general population. Psychometric properties of the scale, including test-retest reliability and convergent and divergent validity among individuals with severe mental illness are supported [70].

Additionally, to characterize the sample and assess change in neuropsychological functioning, neuropsychological assessment measures will be administered, including the Trail Making Tests A and B (mental flexibility, set-shifting) [71], Test d2 (selective attention) [72], Story Recall subtest of the Rivermead Behavioural Memory Test (short- and long-term verbal memory) [73], and the German Vocabulary Test (*Wortschatztest*; premorbid intelligence) [74].

#### Intervention

To ensure comparability of results, both interventions are implemented for the same duration (6 weeks; 12 sessions) and frequency (45–60 min per session). Psychologists undergoing post-graduate training provide both MCT+ and computerized CR. All MCT+ trainers completed a 2-day MCT+ workshop and receive regular intervision from two of the authors of the MCT+ therapy program (RV, FB).

##### Individualized metacognitive therapy program (MCT+)

The main aim of MCT+ is to “plant the seed of doubt” regarding rigid delusional convictions and to encourage patients to critically reflect, extend and change their approach to problem solving. Importantly, patients are not to be “talked out” out their symptoms as this can lead to an escalation of cognitive biases and, thus, increased symptoms. Rather, symptoms are first normalized and an individualized plan for addressing symptoms and cognitive biases is formulated based specifically on each patient’s presenting problems and goals. The second edition of the German manual by [name] et al. was provided to all study trainers (MCT+ materials can be obtained by contacting the authors) [75]. The major changes to the updated manual are the addition of elements regarding stigma and of a new unit focused on self-esteem. An overview of the MCT+ units is provided in Table 3. All of the MCT+ therapy units that focus on cognitive biases (i.e., Therapy Unit 4: Attributional Style; Therapy Unit 5: Decision Making; Therapy Unit 6: Changing Beliefs; Therapy Unit 7: Empathizing; Therapy Unit 8: Memory and Certainty of Judgment) first highlight the fallibility of cognition in general and discuss specific problematic exaggerations of these cognitive processes in individuals with schizophrenia. In a second step, the relationship between cognitive biases, symptoms and their consequences for everyday life, as well as the course of the illness, are emphasized.

**Table 3 Tab3:** MCT+ therapy units

Unit	Description	Exercise/Therapy worksheet examples
1. Case History Questionnaire	The patient’s case history including current problems and symptoms, as well as previous treatments, are gathered through a clinical interview. The patient’s level of motivation is evaluated and the importance of the therapeutic relationship is discussed.	With the use of worksheets, the therapist and patient identify the patient’s current problems, including delusions or hallucinations and to what extent the patient is certain of this belief. Interpersonal or coping difficulties resulting from the delusion/hallucination are identified.
2. Introduction to MCT+	Information about MCT+ and the main therapeutic strategies are discussed. A secondary goal is to develop an understanding of the patient’s problem areas and possible therapeutic targets.	An overview of the therapy program is provided and the patient’s goals are determined with help from therapy worksheets. Patients are asked to identify current or past symptoms and how distressed they are (have been) by these symptoms.
3. Case Formulation	An individual vulnerability-stress-model is created utilizing a “fire” metaphor. For patients with limited illness insight who may be overwhelmed by such a discussion or may be unable to accept explanations for their symptoms, this therapy unit can also be completed toward the end of the training.	Using therapy worksheets the “fire” metaphor is personalized. Vulnerability factors (e.g., genetic predisposition) are compared to wood or coals, while factors that contribute to a first psychotic episode (e.g., stress), are likened to a spark, which ignites the flames. Interventions, which help to reduce symptoms (e.g., psychotherapy), are the “fire extinguisher.”
4. Attributional Style	The goal is to help patients understand that complex social situations can rarely be attributed to one cause (i.e., mono-causal attributions), but are rather the outcome of many factors (myself, other people, circumstances). It is important to help patients gain insight to situations in which they themselves tend to make one-sided attributions, and how certain attributions (especially personalization and blame) reinforce delusions.	Using fictional and, if possible, personal real-life examples, patients are encouraged to identify multiple causes of events that may otherwise be attributed to psychosis-related factors (e.g., a strange smell means that I am being poisoned rather than the possibility that there was a chemical spill or I am in an unfamiliar area where smells may be new). A “card trick” exercise is used to illustrate that there are often simple explanations for strange experiences.
5. Decision Making	Jumping to conclusions can lead to suboptimal decisions, sometimes with dramatic consequences. Patients are encouraged to reflect on whether they currently, or in the past, have made decisions too hastily, and if their delusions were caused or strengthened by these “short-circuit” thinking patterns. Patients should learn to consider the pros and cons of making strong assumptions and to always be open to alternative explanations.	Patients are shown, for example, slides of line drawings in which the details of the figure become increasing clear with each slide. The patient is asked to indicate when they are certain that they know what is depicted. Early responses are often incorrect as not enough details are present to reach a clear decision.
6. Changing Beliefs	Being stubborn and inflexible at times is part of human nature and can actually be helpful to ensure a certain amount of stability so that we do not instantly question everything and everyone. However, being overly fixated can lead to problems too, especially if one’s convictions are wrong.	Pictures, which depict a story, are shown to the patient in reverse order (i.e., the last pictures is shown first). The patient is asked to indicate when they are certain that they know the correct beginning of the story. Often reaching a decision with incomplete information leads to an incorrect response.
7. Empathizing	“To err is human”, especially when it comes to assessing the motives of others. It is emphasized that we cannot infer what another person’s emotional state is from facial expressions or nonverbal signals alone. To become more certain about our interpretation, patients are encouraged to consult additional sources (e.g., contextual factors, previous knowledge of the person). Patients learn that social perceptions are often influenced by personal feelings and people often tend to confuse their inner emotional world with the outside world (e.g., when anxious, a patient may think: “Everybody is against me”). "Unwritten social rules” are also discussed with the patient. The relationship to delusions should be carefully clarified.	The patient is shown a series of pictures and is asked to guess how the person is feeling or what they are thinking. It is emphasized that it is often difficult to know how another person is feeling and that additional information should be sought to avoid making incorrect assumptions. The patient is asked to identify situations in which they were uncertain of how others were feeling.
8. Memory and Certainty of Judgment	The potential for memory biases are discussed and normalized. It is always important to consider the possibility that vague memories might be false, and therefore, should be investigated further by asking others or consulting documents as false memories can have potentially serious consequences (e.g., conflict).	Patients are briefly shown complex scenes with many objects and are then asked to identify which objects were present in the scene. It is discussed with the patient that, like all humans, their memory may not always be perfect and details are often added or omitted based on previous experiences or “common sense” (i.e., false memories).
9. Depression and Thinking	This unit focuses on improving self-perceptions and improving or maintaining social relationships with others. Depression is not “unavoidable” or innate, but tends to be promoted and maintained through certain thought distortions, which can be changed. Therapists help patients to become more aware of if and when they tend to have depressive thought distortions and how their personal depressive symptoms or delusions were intensified or perhaps caused by such thoughts. The extent to which psychosis has an effect on self-esteem is also discussed.	With the help of fictional and, if possible, personal real-life examples, patients are asked to identify alternative, more helpful thoughts for various situations when one might use “black and white thinking” or “should” statements (e.g., when receiving negative feedback from a boss).
10. Self-Esteem	Self-esteem is defined in MCT+ as something that one largely subjectively determines and actually has little to do with the opinions of others. The therapist carefully addresses the different influences that psychotic symptoms can have on one’s self-esteem (excitement and a feeling of being important versus anxiety and guilt), while also recognizing that these symptoms can also partially serve a social function. Using the metaphor of an “inner critic” and a “well-meaning companion,” it is carefully suggested that sometimes content from auditory hallucinations can reflect inner conflicts.	The patient is encouraged to identify personal strengths, especially in areas, which are often not noticed or thought of as self-evident. Concrete situations in which these strengths have been demonstrated are identified.
11. Dealing with the Diagnosis and Relapse Prevention	Based on information gained throughout the 6 weeks, patients are given information about their disorder and how to cope with the diagnosis in everyday life, especially regarding communication of information about the disorder in social situations. Patients are made aware of possible ways the disorder may progress. It can also be beneficial to involve relatives in this final session because they often recognize prodromal symptoms earlier on than patients.	An emergency plan is created in cooperation with the patient, which clarifies whom the patient should seek in case of a crisis (e.g., an institution that the patient trusts, a therapist). Stress reducing and coping strategies are discussed. It is also discussed with the patient in which situations revealing their diagnosis may be helpful or unhelpful.

Although the MCT+ units are presented in the order provided in Table 3, it is emphasized that treatment should be tailored to the individual needs and insight level of the patient, as well as trainer preferences. As such, more time can be spent on any one unit and themes can be skipped completely. For the purposes of the RCT, all trainers were instructed to complete the first therapy units focused on discussion of the importance of trust and openness to the therapeutic relationship and taking a case history (Therapy Unit 1), introducing MCT+ (Therapy Unit 2) and developing a personal illness model (Therapy Unit 3; when appropriate, this unit can also be completed at a later stage during therapy). In addition, trainers are to choose at least two units addressing cognitive biases. There are also two units devoted to affective problems (Therapy Unit 9: Depression and Thinking; Therapy Unit 10: Self-Esteem). In the last unit, focus is on coping with (the stigma of) illness, preparing patients for the discontinuation of therapy and discussing relapse prevention strategies (Therapy Unit 11). Each unit includes a number of therapy demonstrations, as well as worksheets displaying discussion topics and exercises that serve to illustrate the main topic. Certain exercises (e.g., card trick in Therapy Unit 4) are preferably presented with the help of a computer laptop or tablet.

In addition, most sessions include “between-session” tasks (i.e., homework) to encourage application and practice of skills in daily life. Homework is then discussed at the beginning of the following session. Given that many patients with psychosis have difficulties remembering and organizing information, in the last session participants are given a booklet of copies of important MCT+ therapy demonstration sheets that were presented during the treatment so that they have a “self-help” booklet to review after therapy has ended. Additionally, postcards are sent to the participants three months after the final session to inquire whether they have been using the skills learned in MCT+. Although participants are not allowed to respond to the mailing, they are encouraged to look at their booklets and review the MCT+ materials.

